### Data analyses

All primary analyses will be carried out on an intent-to-treat (ITT) basis, i.e., all subjects randomized will be analyzed according to the treatment they were assigned regardless of adherence to treatment. Level of fidelity to training intensity, accounting for adherence, will be controlled for in these analyses. All statistical tests will be two-sided with critical value α = 5%.

Mixed effects regression will be used to model suicide risk as a function of time (0, 6, 12 weeks), treatment group (AE or ST), interaction of time by treatment group, and site (1, 2, 3, or 4). The efficacy of AE to improve suicide risk in people with SZ will be represented by the statistical significance of the time by treatment group interaction. The effect of AE on mood, sleep, and executive functions will be tested by conducting similar analyses, i.e., mixed effects regression across 0, 6, and 12 weeks.

Mediators in the relationship between AE and suicide risk will be identified by multi-step process. A mediation effect will be estimated by taking the expected value of the total effect of AE on changes in suicide risk and subtracting the effect when changes in mood, sleep, and executive functioning have been controlled. These mediation effects will be tested by fitting a Structural Equation Model (SEM) with change in depressed mood, sleep, and executive function from baseline to 6 weeks as mediators of the relationship between AE treatment and change in suicide risk from baseline to 6 weeks as well as later changes in suicide risk from 6 to 12 weeks using MPlus version 8. The mediator-outcome relationship can be confounded by other time-varying covariates (e.g., BMI changes), and these will also be adjusted for in the model.

Change in suicide risk from baseline will be modeled using mixed effect regression predicted by contemporaneous change in aerobic fitness from baseline as measured by VO_2_max tests (at 6 and 12 weeks), controlling for treatment group and other covariates. The ability of aerobic fitness improvement to predict reduction in suicide risk will be represented by a statistically significant positive regression coefficient for change in aerobic fitness.

Demographic and other biologically relevant baseline variables (e.g., sex, depression, and smoking status) will be included as control variables if there is evidence of randomization imbalance in them. Multiple imputation will be used to handle missing data using the MI and MIANALYZE SAS procedures.

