Intensity of training in the AE condition will be individualized to each participant based on his/her maximal heart rate as determined during the VO_2_max test conducted at baseline. During week 1, training will aim to maintain the participant’s HR at 60% of their max HR. This goal will increase to 65% in week 2, 70% in week 3, and 75% for the remainder of the 12 weeks. HR will be monitored using Polar V800 HR monitors (a digital watch connected to a Bluetooth-enabled H10 sensor strap) that participants will wear during sessions [50]. The monitors will be programmed to emit a soft beeping sound when the participant’s HR drops below the individually-targeted weekly AE intensity level. In this case, the trainer will encourage him/her to achieve their target goal. At session’s end, the data is uploaded from the monitors to a computer and analyzed using Polar Flow Sync software.

The stretching and toning (ST) condition is designed to replicate the variables of the AE condition such as schedule, duration, facilities, format, trainer contact, and social interactions without affecting aerobic fitness. Similarly to the AE training sessions, ST sessions will begin with a 10-min warm-up period led by the trainer. The following 45-min of each session will consist of a mixture of static stretching positions, low-impact toning exercises, and yoga- and tai chi-inspired routines using the Xbox Kinect. ST exercises are recommended by American College of Sports Medicine (ASCM) guidelines to improve flexibility [45, 46]. To maintain interest, new exercises will be introduced every week. While static stretching may result in limited transient HR increases, it provides limited aerobic fitness benefits [51–54]. Just as in the AE condition, each ST session will end with a trainer-led 5-min cool-down period.

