Intensity of training in the ST condition will also be individualized per participant based on his/her maximal heart rate as determined during the VO_2_max test conducted at baseline. However, the training will aim to keep the participant’s HR below 60% of their max HR. HR will be monitored using Polar V800 HR monitors (a digital watch connected to a Bluetooth-enabled H10 sensor strap) that participants will wear during sessions [50]. The monitors will be programmed to emit a soft beeping sound when the participant’s HR exceeds the individually calculated ST maximum intensity level. In this case, the trainer will encourage him/her to rest until his/her HR lowers adequately. At session’s end, the data is uploaded from the monitors to a computer and analyzed using Polar Flow Sync software.

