### Training fidelity

In both training conditions, training fidelity will be monitored and indexed by (1) the number of sessions attended and (2) the number of minutes per session the participant trained with his/her HR above (for AE condition) or below (for ST condition) the designated training intensity. The in-session training intensity is included to address the possibility that participants may attend the sessions but exercise too lightly (for AE condition) or too intensely (for ST condition).

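### The primary analyses are defined as intent-to-treat and the listed model omits training fidelity, yet the plan also says that fidelity will be controlled for in them

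*Protocol article*

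**What the plan says.** Three statements in the protocol article's Data analyses section bear on the primary analysis.

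- The analysis principle is intent-to-treat: "all subjects randomized will be analyzed according to the treatment they were assigned regardless of adherence to treatment".
- The next sentence adds an adjustment: "Level of fidelity to training intensity, accounting for adherence, will be controlled for in these analyses". The only analyses it can refer to are the primary ones just named.
- The following paragraph gives the model for suicide risk: time, treatment group, "interaction of time by treatment group, and site (1, 2, 3, or 4"). Fidelity is not a term. Efficacy is judged by the time-by-group interaction.

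The Training fidelity section defines the covariate. Its first component is attendance: "training fidelity will be monitored and indexed by (1) the number of sessions attended". Its second is the number of minutes per session that "the participant trained with his/her HR above (for AE condition) or below (for ST condition) the designated training intensity".

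The Interventions section gives the two criteria. The AE target starts at 60% of maximal heart rate, and then: "This goal will increase to 65% in week 2, 70% in week 3, and 75% for the remainder of the 12 weeks". In the ST arm "the training will aim to keep the participant’s HR below 60% of their max HR".

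No section confines the fidelity adjustment to a secondary or sensitivity analysis.

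**The concern.** Sessions attended and minutes in the heart-rate zone are known only after randomisation. Both can depend on the arm and on the participant's state of mind: a more depressed participant may attend less or train more lightly. In the AE arm, fidelity is also close to the delivered dose, the route by which fitness, and through it suicide risk (Hypothesis 1.2), is expected to change.

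The covariate is also not the same quantity in both arms. Thirty minutes of fidelity means thirty minutes above a rising target in AE and thirty minutes under a fixed ceiling in ST. Comparing the arms at equal fidelity has no clear meaning and is not protected by randomisation.

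At stake is which model produces the primary p-value, and whether that p-value belongs to the randomised comparison.

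**Working it through.** **1. The texts side by side.** The intent-to-treat sentence excludes adherence from the comparison. The fidelity sentence brings it back. The model sentence leaves it out. An analyst could follow either of the last two and claim to follow the plan.

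**2. The plan's only power figure.** The contested sentence carries no number. The Sample size calculations section states more than 80% power for the parent study, with 80 per arm and 0.50 SD. Noncentrality is 0.50 × √(80/2) = 3.16, and Φ(3.16 − 1.96) = 88.5% (88.2% by the noncentral t). The figure reproduces and gives a benchmark for the unadjusted analysis below.

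**3. Change-score check.** From the documents: 160 participants allocated 1:1, so 80 per arm; two-sided α of 5%; 0.50 SD as the parent study's target. Assumed, because the documents give no values: mean fidelity in AE/ST of 30/30, 25/35 or 20/40 minutes; SD 10; correlation λ of 0.3 or 0.5 between fidelity and a prognostic factor; correlation γ of 0, 0.2 or 0.4 (in absolute value) between that factor and the 12-week change (SD 1).

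Within an arm, the slope of change in risk on fidelity is −γλ/10 per minute. The adjusted group coefficient is therefore shifted from the true effect by approximately

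shift = γλ × (AE mean − ST mean)/10.

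Simulation under no true effect (2,000 runs per cell; Monte Carlo standard error near 5% is √(0.05 × 0.95/2000) = 0.5 points):

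| AE/ST min | γ | λ | Formula | Simulated | Type I error, adjusted |
|---|---|---|---|---|---|
| 25/35 | 0.2 | 0.3 | −0.06 | −0.058 | 5.9% |
| 25/35 | 0.2 | 0.5 | −0.10 | −0.098 | 9.3% |
| 25/35 | 0.4 | 0.3 | −0.12 | −0.124 | 10.5% |
| 25/35 | 0.4 | 0.5 | −0.20 | −0.196 | 20.1% |
| 20/40 | 0.2 | 0.3 | −0.12 | −0.119 | 7.7% |
| 20/40 | 0.2 | 0.5 | −0.20 | −0.201 | 14.2% |
| 20/40 | 0.4 | 0.3 | −0.24 | −0.239 | 18.8% |
| 20/40 | 0.4 | 0.5 | −0.40 | −0.398 | 42.8% |

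- Without fidelity, type I error was 4.0% to 5.4% in every null cell.
- With equal means (30/30), the adjusted and unadjusted results agreed: no material shift.
- With a true effect of −0.50, the adjusted estimate ran from −0.56 to −0.91 in the same eight settings.
- With γ = 0 there was no bias, but power fell from about 88% to 79% (25/35) or 59% (20/40).
- By the formula, the shift changes sign if mean fidelity is higher in AE.

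**4. Check on the planned type of model.** The plan tests time by group in repeated measures, not a single change score. One dataset per scenario was generated with 800 per arm, weeks 0, 6 and 12, 25/35 minutes, γ = 0.4 and λ = 0.5. Time was scored 0 to 1, so the coefficient is the group difference in 12-week change. The models had no site term.

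| How fidelity enters | True effect 0 | True effect −0.50 |
|---|---|---|
| Not at all | −0.03 | −0.49 |
| Time-invariant main effect | −0.03 | −0.49 |
| Time-varying, 0 at baseline | −0.10 | −0.54 |
| With fidelity × time | −0.26 | −0.70 |

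Standard errors are about 0.045 to 0.05; the comparison that matters is between rows fitted to the same data. With prognosis-related dropout at week 12, the first two rows still agreed to within 0.001.

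**The case against.** The strongest reply is that the model actually written down omits fidelity and that efficacy rests on the time-by-group term of that model. If fidelity were added as a single main effect, that term would hardly move. How a covariate enters is a detail that a condensed article may leave to the full protocol or analysis plan. The simulated sizes rest on fidelity means and correlations that appear nowhere in the documents.

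Most of this stands, and it limits the consequence. A reader might infer that the reported AE effect will no longer be the randomised comparison, or that a large false-positive rate is established. The documents do not support that: they do not settle whether fidelity enters the efficacy model or in what form, and they give no fidelity data by arm. A reader might also infer that fidelity is scored in opposite directions. It is not shown to be: in both arms more minutes means better compliance with the assigned condition. What differs is the heart-rate criterion.

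The reply does not rescue the sentence. It is a stated rule, not an omitted detail, and it contradicts the sentence before it. In the one form examined that does no harm, it also does nothing.

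**Conclusion.** The sentence is wrong as written. The section promises intent-to-treat regardless of adherence and lists a model without fidelity, yet says fidelity will be controlled for. Fidelity is a post-randomisation variable measured against different criteria by arm, so conditioning on it does not in general estimate the randomised contrast. That much rests on the text alone.

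The size of the harm is conditional. It needs fidelity to enter as a time-varying term, with a time interaction or in a change-score model, and it needs fidelity both to differ by arm and to share causes with suicide risk. Under the assumed inputs, the change-score null shift is about 0.06 to 0.40 SD and type I error about 6% to 43%. The lower end is barely distinguishable from 5%, and the upper end is the most extreme combination tried. The range is illustrative and is not a forecast for this trial.

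**What to change.** Delete the fidelity sentence for the primary intent-to-treat analyses and state that the primary model is the one listed (time, group, time by group, site), with no post-randomisation covariates. The separately described fitness and mediation models are not affected.

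Report both fidelity components descriptively by arm. Put any fidelity or dose-response analysis in a separately labelled exploratory section that says it is not protected by randomisation; this applies equally to a dose-response analysis within the AE arm. A complier-average analysis would need more than a label: ST is an active control with its own attendance and intensity, so compliance must be defined in both arms and the exclusion restriction stated.

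The cost is one deleted sentence and a short statement of the exploratory analyses. No data collection changes and participants bear no burden.

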### Eligibility criteria

Inclusion Criteria: 18–55 years of age; DSM-V diagnoses of SZ, schizoaffective disorder, or schizophreniform disorder; taking an antipsychotic medication for at least 8 weeks and on current dose for 4 weeks and/or taking an injectable depot antipsychotic with no change in last 3 months; medically cleared by a physician to take part in VO_2_max tests and AE/ST training; capacity to understand all the potential risks and benefits of the study; and consented to participate in the parent R01 study (“Improving Cognition via Exercise in Schizophrenia”; MH110623; PIs: [name] & [name]) which aims to assess the impact of AE on cognitive and daily functioning in people with SZ.

Exclusion Criteria: DSM-IV diagnosis of alcohol/substance abuse (except nicotine) within the last month or a diagnosis of alcohol/substance dependence (except nicotine) within the last 6 months; initiation of anti-depressants, mood stabilizers, or other medications known to impact cognition in previous 4 weeks or any changes in doses during this period; history of seizures/head trauma with loss of consciousness (> 10 min) resulting in cognitive sequelae; significant clinical abnormalities in physical examination, lab assessments, or ECG; neurological/medical conditions that could interfere with study participation (e.g., AIDS, unstable cardiac disease, stuttering); BMI ≥ 40; untreated hyper- or hypothyroidism; pregnant/nursing; serious homicidal risk (past 6 months); “moderate” or more severe conceptual disorganization (PANSS ≥ 4); poor English reading ability (WTAR< 7); and participation in a study with cognitive assessment in the past 3 months.

This study has been approved by the institutional review board of the Icahn School of Medicine at Mount Sinai, New York, NY; University of North Carolina, Chapel Hill, NC; Stanford University, Stanford, CA; and Augusta University, Augusta, GA. As part of the informed consent process, the rationale of the study and its methods will be described in detail and all questions will be answered. All participants will be asked to provide written informed consent before participation.

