### Suicide risk safety

To address potential safety concerns associated with recruitment of individuals with higher suicide risk, all participants will also be administered a suicide risk assessment (i.e., C-SSRS) by phone at 3 and 9 weeks after baseline, in addition to the suicide risk assessments scheduled during research visits at baseline, 6 weeks, and 12 weeks. All assessments will capture suicidal symptoms from the last administration of the instrument. The raters will consult with the site PI regarding the detection of any suicidality, including passive suicidality. Any subject with a C-SSRS score equal or greater than “4” (Active Suicidal Ideation with Some Intent to Act, without Specific Plan) will require a consultation with [name], the project’s Medical Director, and [name], the project’s suicide expert. Any subject that scores a “5” (Active Suicidal Ideation with Specific Plan and Intent) and judged to be actively suicidal will require urgent clinical evaluation for the possibility of hospitalization, and he/she will be escorted to the closest ER by study staff. [name] has extensive clinical experience treating veterans at high risk for suicide and is available by cell phone 24/7, should clinical consultation regarding study participants be necessary.

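### The primary test uses the baseline C-SSRS as an outcome time and not as a covariate, which gives away power that the trial could have at no cost

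*Protocol article*

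**What the plan says.** **Primary model.** In the protocol article, Data analyses, the primary model is "Mixed effects regression will be used to model suicide risk as a function of time (0, 6, 12 weeks), treatment group (AE or ST"), together with the time-by-group interaction and site. Efficacy is "represented by the statistical significance of the time by treatment group interaction". Mood, sleep and executive function are handled by "conducting similar analyses, i.e., mixed effects regression across 0, 6, and 12 weeks". No distribution or link is named, and it is not said whether time is categorical or linear.

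**Baseline covariates.** The closing paragraph of the same section brings in baseline variables only where the arms look imbalanced after randomization. Its examples are sex, depression and smoking status. Baseline suicide risk is not named as a covariate of the primary model.

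**Change scores.** These are explicit only elsewhere: in the mediation model, and in the fitness analysis for Hypothesis 1.2 ("Change in suicide risk from baseline will be modeled using mixed effect regression predicted by contemporaneous change in aerobic fitness").

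**Outcome and population.** The Suicide risk section describes the C-SSRS as an interview covering four domains. The Suicide risk safety section sets a consultation rule ("Any subject with a C-SSRS score equal or greater than" level 4) whose levels are ordered verbal categories. The Eligibility criteria cover age, diagnosis, stable antipsychotic treatment, being "medically cleared by a physician to take part in VO_2_max tests and AE/ST training" and similar conditions. They contain no suicide-risk criterion in either direction.

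**Power.** The Sample size calculations section reports no power for the C-SSRS. It gives only the parent study's figure for cognition.

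**The concern.** Under randomization the two arms have the same expected baseline. A model that gives each arm its own free baseline mean at week 0, and then tests how the arms diverge, subtracts an estimated baseline difference that is pure noise. Conditioning on baseline removes only the part of that noise that predicts follow-up, so its variance is never larger in the standard continuous case.

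This matters more here than usual, for two reasons. No power was calculated for the primary outcome, so there is no known margin to spend. And because nobody is selected for suicidality, a sizeable share may score at the bottom of the scale at baseline and cannot improve. Differences in change are then noisy while the attainable effect is small. What is at stake is the chance of detecting a real effect under Hypothesis 1.1.

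**Working it through.** **1. The only stated power figure.** The parent study has 80 completers per arm (100 × 0.8), a 0.50 SD difference and two-sided 5%:

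Φ(0.5 × √(80/2) − 1.960) = Φ(3.162 − 1.960) = Φ(1.202) = 88.5%.

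This agrees with the stated figure of more than 80%, but it concerns the cognitive composite. This study plans 160 participants, or 80 per arm. If the 20% loss applies to them, 80 × 0.8 = 64 per arm remain, and the same formula gives Φ(2.828 − 1.960) = 80.7%.

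**2. What the interaction estimates.** With complete data, the categorical-time interaction at week 12 is (AE week 12 − AE week 0) − (ST week 12 − ST week 0), a difference in change. If time is linear, three equally spaced visits carry slope weights −1, 0, 1, so the slope comparison is the same contrast.

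**3. Closed form, continuous outcome with equal variances.** The per-person variance is 2σ²(1 − ρ) for change and σ²(1 − ρ²) for baseline adjustment. The ratio is 2(1 − ρ)/(1 − ρ²) = 2/(1 + ρ). The power columns assume 0.5 SD and are written as change / adjusted.

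| ρ | Ratio | Power, 80 per arm | Power, 64 per arm |
|---|---|---|---|
| 0.3 | 1.54 | 76.2% / 91.2% | 66.7% / 84.3% |
| 0.5 | 1.33 | 88.5% / 95.5% | 80.7% / 90.4% |
| 0.7 | 1.18 | 98.3% / 99.3% | 95.5% / 97.7% |

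**4. Illustrative simulation, ordered score with a floor.** These inputs are all assumptions:
- six levels (0–5) cut from a latent normal, with the share above zero halving from level to level;
- latent correlation 0.6 between visits;
- odds ratio 2.0 or 2.5, entered as a latent shift of ln(OR)/1.7 = 0.41 or 0.54, with half present at week 6 and all at week 12;
- complete data, site ignored, 4,000 runs per setting.

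The planned contrast comes from a random-intercept model. The comparator is a linear model of week 12 on treatment and baseline.

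| Per arm | At zero | OR | Week-12 interaction contrast | Baseline-adjusted linear | Loss (points) |
|---|---|---|---|---|---|
| 80 | 50% | 2.0 | 53.4% | 70.6% | 17.2 |
| 80 | 50% | 2.5 | 74.8% | 90.8% | 16.0 |
| 80 | 70% | 2.0 | 38.6% | 54.8% | 16.2 |
| 80 | 70% | 2.5 | 54.1% | 76.5% | 22.4 |
| 80 | 85% | 2.0 | 22.6% | 34.3% | 11.7 |
| 80 | 85% | 2.5 | 32.1% | 52.0% | 19.9 |
| 64 | 50% | 2.0 | 45.1% | 60.2% | 15.1 |
| 64 | 50% | 2.5 | 63.9% | 82.1% | 18.2 |
| 64 | 70% | 2.0 | 32.2% | 46.4% | 14.2 |
| 64 | 70% | 2.5 | 44.2% | 65.4% | 21.2 |
| 64 | 85% | 2.0 | 19.3% | 28.0% | 8.7 |
| 64 | 85% | 2.5 | 26.0% | 41.0% | 15.0 |

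Read as a joint 2-df test, the interaction does worse: 42.5%, 29.7% and 16.8% at 80 per arm, OR 2.0 and 50%, 70% and 85% at zero.

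**5. Type I error (OR 1, same runs).** It was 4.6–5.7% for the two interaction tests and 4.4–6.1% for the adjusted model; Monte Carlo error is √(0.05 × 0.95/4000) ≈ 0.3 points. The 6.1% arose at 80 per arm with 50% at zero. A separate 600-run set gave 5.2% in that setting.

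**6. Correlation and the ordinal link.** This 600-run set (error about 2 points) used baseline and week 12 only. At 80 per arm, 70% at zero and OR 2.0, change versus baseline-adjusted linear gave 31.7% versus 46.2% at correlation 0.4, and 56.3% versus 70.0% at 0.8. Across all its non-null settings, moving from baseline-adjusted linear to baseline-adjusted proportional odds changed power by −1 to +9 points. The gain was largest at the heaviest floor.

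**The case against.** The best defence is that the article is a condensed account. It names no link or distribution, so an ordinal mixed model would fit its words, and such details are commonly left to a fuller plan. That stands. A reader might infer, from the shared model for mood, sleep and executive function and from differences taken elsewhere, that the C-SSRS is to be analysed as an interval score. The text does not say so.

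A reader might also infer that the primary analysis uses change scores. It does not: those belong to Hypothesis 1.2 and the mediation model. The primary contrast is only equivalent to a difference in change when data are complete.

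The floor is likewise unproven. No baseline distribution is given, no C-SSRS summary score is named, and the six levels are borrowed from the safety categories. The safety text itself speaks of recruiting people at higher suicide risk. Equally, the eligibility list does not exclude suicidal participants.

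Finally, keeping baseline as a response retains participants who have only a baseline visit. That advantage is real, but it does not need free baseline means; the constrained version keeps it.

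None of this touches the core. Week 0 as an outcome time and the interaction as the efficacy test are both stated, and baseline suicide risk is not a planned covariate.

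**Conclusion.** The point holds as one of efficiency. The planned week-12 contrast has higher variance than a baseline-adjusted one for any correlation below 1 in the continuous case, by 18% to 54% for ρ from 0.7 down to 0.3. It lost about 9 to 22 power points in the 4,000-run settings. The direction is firm; the size rests on assumed floor share, correlation, odds ratio and number of levels, and on complete data with site ignored.

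Two stronger readings are not supported. One is that the test is invalid: the simulated type I error of the interaction tests stayed near nominal. The other is that the C-SSRS must have an ordinal primary model: most of the gain comes from conditioning on baseline, and the ordinal link adds only a few points, about none in one setting. Hypothesis 1.1 is also not the only hypothesis on suicide risk, since 1.2 and 2.2 concern it too, but it is the one this test serves.

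**What to change.** Name the C-SSRS score to be analysed. Model it at weeks 6 and 12 with baseline score as a prespecified covariate, plus treatment, visit, treatment-by-visit and site. Alternatively, keep all three visits and constrain the arms' baseline means to be equal. State that the week-12 treatment contrast is the test of Hypothesis 1.1, in place of the general interaction. The same wording can serve the Hypothesis 2.1 outcomes.

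Because the C-SSRS levels are ordered, add a baseline-adjusted ordinal mixed model as a sensitivity analysis. Its drawbacks are the proportional-odds assumption, sparse upper categories, and an odds ratio in place of a mean difference.

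The cost is a few lines of analysis text and minor programming. Baseline C-SSRS is already collected, so no visit, measure or participant is added. If baseline becomes a covariate, participants without a week-6 or week-12 score contribute only through the multiple imputation already planned.

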## Randomization

After signing informed consent and undergoing baseline assessment of primary and secondary outcome measures, eligible participants will be assigned 1:1 randomly via computer to one of two 12-week, 3×/week, 1-h interventions: (1) aerobic exercise intervention (AE) or (2) a stretching and toning control intervention (ST). Participants will receive intervention assignment via a secure telephone call.

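### Site enters the primary model only as a main effect, so in a linear model it does nothing to the time-by-group efficacy test, and baseline control variables entered the same way would not either

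*Protocol article*

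**What the plan says.** The Data analyses section of the protocol article names the terms of the primary mixed effects regression: time (0, 6 and 12 weeks), then "treatment group (AE or ST), interaction of time by treatment group, and site (1, 2, 3, or 4". The only interaction listed is time by group. The same section fixes the criterion: efficacy "will be represented by the statistical significance of the time by treatment group interaction".

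Baseline variables, with sex, depression and smoking as examples, "will be included as control variables if there is evidence of randomization imbalance in them". Whether they enter as main effects or with a time interaction is not stated. On missing data: "Multiple imputation will be used to handle missing data using the MI and MIANALYZE SAS procedures". Mood, sleep and executive function are to be analysed in a similar way.

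A further control is announced for the primary analyses: "Level of fidelity to training intensity, accounting for adherence, will be controlled for in these analyses". Its form is not stated either, but the Training fidelity section records "the number of minutes per session the participant trained with his/her HR above (for AE condition) or below (for ST condition) the designated training intensity", so it could be entered as a quantity that changes over time.

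**The concern.** A reader will take a site term, and control variables added after an imbalance, to adjust the efficacy result. As written, the site term cannot do so in a linear model. It is a constant shift per participant, whereas the tested term concerns differences between a participant's own visits. The section's stated response to baseline imbalance would fail in the same way if it follows the form used for site. Depression is one of the protocol's own examples, and its Background names depressive mood as a predictor of completed suicide. If baseline depression were unevenly distributed and predicted change in suicide risk, the efficacy estimate would carry the full effect of that imbalance. Likewise, any difference between the four sites in how suicide risk changes would stay in the error term.

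**Working it through.** **The plan's own figure.** None bears on this point. The only power statement (Sample size calculations) concerns cognition in the parent study: 80 per arm, 0.50 SD, two-sided 5%. Power = Φ(0.50 × √(80/2) − 1.96) = Φ(1.20) = 88.5%, consistent with the stated figure of over 80%. It says nothing about suicide risk or covariate adjustment.

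**Algebra.** Let G be treatment group, X a baseline variable, σ_s the site effect and u_i the participant effect:

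Y_it = a + τ_t + γG_i + δ_tG_i + σ_s + κX_i + u_i + e_it, with τ_0 = δ_0 = 0.

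Subtract baseline from week 12:

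Y_i,12 − Y_i,0 = τ_12 + δ_12G_i + (e_i,12 − e_i,0).

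σ_s and κX_i have gone. With all visits present, the estimate of δ_12 is the difference between arms in mean change, and its standard error comes from the spread of the changes. The level of the scores adds nothing, because it has its own free intercept and group coefficient. If the site and covariate effects may differ by visit (σ_s,t and κ_t), then (σ_s,12 − σ_s,0) and (κ_12 − κ_0)X_i remain in the change, and the adjustment acts.

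**Numerical check.** From the documents: 160 participants, three visits, four sites, 1:1 allocation. Assumed, because the documents give no values: all variances and effects, a covariate shifted by 0.3 SD in one arm, and a covariate and sites that predict change. Interaction estimate (SE), one simulated data set:

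| Fit | No covariates | Site + covariate, main effects | Both by time |
|---|---|---|---|
| Complete, random intercept | −0.44593 (0.18523) | −0.44593 (0.18523) | −0.47818 (0.16667) |
| Complete, unstructured | −0.44593 (0.21916) | −0.44593 (0.21916) | −0.47818 (0.18450) |
| Complete, random slope, linear time | −0.22297 (0.10958) | −0.22297 (0.10958) | −0.23909 (0.09225) |
| 20% dropout, 10 imputations | −0.47312 (0.22762) | −0.47312 (0.22762) | −0.51430 (0.20669) |

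The main effects moved only the group coefficient at baseline, which is not the test (random intercept: −0.029 with no covariates, 0.251 with site, 0.024 with both).

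**Where the identity stops.**
- With 20% dropout and no imputation (random intercept), the main effects shifted the estimate by 0.07 SE on average and 0.21 SE at most over 60 data sets in which the covariate did not predict change; the SE ratio was 0.99 to 1.00. In one data set where it did predict change, the shift was (0.35488 − 0.29855)/0.22655 = 0.25 SE.
- Fidelity entered as time-varying changed the complete-data result from −0.446 (0.185) to −0.403 (0.192). Entered as one value per participant, it changed nothing.
- A non-linear link was not computed.

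**What could be at stake, under assumptions only.**
- Imbalance: take a 0.3 SD imbalance, a covariate effect that falls by 0.3 units per SD by week 12, and no true treatment effect. The expected error is 0.3 × (−0.3) = −0.09. Over 300 runs the mean estimate was −0.098 (compound symmetry) and −0.086 (unstructured), both unadjusted and with the main effect, against −0.010 and +0.003 with covariate by time.
- Precision: if the added terms explain a share R² of the variance of change, power from an assumed 80% becomes Φ((0.8416 + 1.96)/√(1 − R²) − 1.96). For R² = 0.05, 0.10, 0.15 and 0.25 this gives 82%, 84%, 86% and 90%.

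**The case against.** The best defence is that nothing invalid is planned. The Randomization section says that "eligible participants will be assigned 1:1 randomly via computer", so the unadjusted comparison of change is valid and unbiased over repeated randomisations. Stable differences in level between sites, or between participants, cancel already. A site main effect is a conventional term, and the protocol never says that it adjusts the efficacy estimate. Only variables that predict change matter, and the documents do not show that site, sex, depression or smoking do so here. All of this stands. It means that a reader who infers a biased or invalid test goes too far: the −0.09 above is conditional on an assumed chance imbalance.

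A reader might also infer that every control variable in the plan is inert. The documents do not support that. Main-effect form is written down for site only; for the baseline variables it is a natural reading but an unstated one. The fidelity control could be time-varying and would then move the result. Nor does the identity cover every mixed model: the protocol does not say that the regression is linear and fixes no link for the suicide-risk score.

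It can also be said that covariate form is detail for an analysis plan. That is fair for the baseline variables taken alone. It does not answer the point on site, because the article itself fixes both the model terms and the tested coefficient, and the result follows from the two together.

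**Conclusion.** The point holds within these limits. In a linear mixed model with complete or multiply imputed visits, site as specified changes neither the estimate nor the standard error of the time-by-group interaction, and baseline control variables entered in the same form would not correct a chance imbalance in the efficacy result. That is algebra and does not depend on the simulated inputs. The test remains valid under randomisation.

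The size of the loss cannot be derived from the documents. They give no variance for change in suicide risk, no site or covariate effect on change, and no power calculation for this outcome. The error of −0.09 and the gains of 2 to 10 percentage points in power are illustrations from assumed values, and the 80% starting point is not this trial's figure. The change is worth making because it can recover precision and correct chance imbalance with data already being collected.

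**What to change.** In the Data analyses section, state that site enters the primary model together with site by time, and that each baseline control variable enters together with its interaction with time. Apply the same form to the similar models for mood, sleep and executive function. The time-by-group interaction remains the efficacy test.

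Site by time uses 3 × 2 = 6 extra parameters if time is categorical, or 3 if it is linear. Each covariate that needs one parameter uses 2 or 1 more. This is small against 160 participants and needs no new data. Modelling only the follow-up scores, with or without baseline as a covariate, is a different analysis with its own estimate and is not an equivalent wording of this change.
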